## Abstract

**Introduction:**

Cardiovascular disease (CVD) is the most common cause of death both globally and in the United Arab Emirates. Despite public health measures and health education, the rates of death from CVD remain stable. Barriers previously identified to lifestyle changes include cultural reasons, boredom, and lack of family support. The Emirates Heart Health Project (EHHP) seeks to support healthy lifestyle changes through a family-based intervention using a health coach and fitness tracker.

**Methods and analysis:**

The EHHP is a stepped-wedge cluster-randomized trial with each cluster comprised of members of an extended family. Eligible participants will be ≥ 18 years of age, with BMI ≥ 25, have Emirati citizenship and be able to give informed consent for study participation. The cluster will have 16 weekly teaching sessions in the participants’ family home by a health coach who will review individual weight, diet and exercise (monitored by a wearable fitness tracker). The clusters will have pre-intervention assessments of their weight and CVD risk profile and enter the intervention in randomized order. Each cluster will have a post-intervention assessment of the same measures. The primary outcome is weight reduction from baseline. Secondary outcomes will include change in CVD risk factors such as systolic and diastolic blood pressure, hemoglobin A1c, total cholesterol, LDL cholesterol, HDL cholesterol and triglycerides, waist circumference, and BMI. A mixed linear model will be used for analysis, where the parameters measured at the end of each 16-week episode will be the outcome values. These will be analyzed such that baseline values (measured just prior to the start of an episode) will be fixed covariables. Random effects are the family units. This trial has been registered with the NIH at clinicaltrials.gov (NCT04688684) and is being reported using the SPIRIT (Standard Protocol Items: Recommendations for Interventional Trials) and TIDieR (Template for intervention description and replication) framework.

**Trial registration:**

Clinicaltrials.gov NCT04688684.

## Introduction

Non-communicable diseases overtook infectious diseases as the leading cause of death in the past century, and despite concerted efforts, continue to result in the deaths of millions worldwide each year. Despite methodological challenges, a growing body of literature gives mixed evidence that links these diseases with modern lifestyles, which include an increased intake of calorie-dense nonnutritive foods combined with a lack of physical activity leading to obesity [1, 2] and overweight [3] which increases the risk of developing cardiovascular disease [4, 5] as well as cancer [6]. These trends are mirrored in the country of the United Arab Emirates (UAE), as well as in the specific location of this clinical trial, the emirate of Abu Dhabi [7, 8].

Citizens of the UAE, called Emiratis, belong to a collectivistic culture centered on the family and the religion of Islam. The UAE has rapidly incorporated cutting-edge technology in both the health and social sectors. For example, the rate of smartphone use penetration is one of the highest in the world at 91% [10], and telemedicine has become part of routine clinical care [11]. At the same time, traditional values have been preserved, such as the extended family gathering weekly for lunch after Friday prayers, which can include dozens of family members. It also remains common to eat together from a communally prepared meal, which makes it challenging to make drastic changes in the individual diet. Modesty is also highly valued, which in some families, along with extreme heat for several months of the year, has limited options for outdoor physical exercise, especially for women.

These factors may at least partially explain why rates of obesity, overweight, and CVD risk factors have remained stable despite greatly expanded screening and referrals to obesity clinics and dieticians in the primary health centers with no out-of-pocket cost. In fact, studies done in the UAE show that despite widespread knowledge of healthy diet and exercise, multiple barriers persist to lifestyle change. The findings of a paper-based survey showed that a sub-optimal diet was the leading risk factor for deaths due to cardio-metabolic disease (CMD) and estimated that this accounted for 72% of CMD deaths in the UAE, which would account for an excess mortality of 444 lives out of the 617 deaths recorded in 2017. In particular, the low consumption of whole grains was responsible for 22% of CMD deaths in the UAE. Other risk factors included high levels of processed meat, red meat, and sugar sweetened beverages [7].

A survey of patients in the UAE with type 2 diabetes showed only 3% met numerous guidelines’ recommendations for 150 minutes of moderate intensity aerobic activity or 75 minutes of vigorous aerobic activity per week [12]. The reasons given for not exercising included cultural reasons (29.2%), “exercise is boring” (20.3%), and lack of family support (4.1%).

Individual appointments are available through primary health centers to access dieticians and physician-led obesity programs, which include the use of lifestyle interventions as well as pharmacologic interventions such as metformin, orlistat, and liraglutide. These services are available at no out-of-pocket cost to Emiratis who meet certain clinical criteria. Despite wide access to these services which comes at significant cost to the health care system, the overall goal of reduction of harm has not been achieved.

The Emirates Heart Health Project (EHHP) is a culturally sensitive, family-based intervention utilizing a health coach and leveraging smartphone and wearable sensor technology to promote lifestyle changes based on the highly successful and durable Diabetes Prevention Program (DPP) curriculum. Given the high rates of smartphone use and openness to technology, it is hypothesized that the use of a wearable fitness tracker will allow for the collection and sharing of physical activity by participants with a health coach and members of the extended family, which may give added motivation and opportunities for positive reinforcement. Instant messaging between participants and the health coach can also allow for ongoing communication such as reminders and addressing challenges to sustained lifestyle change. At the same time, given the central role of family in the decisions individual participants make, a collective commitment on the part of an extended family to eat a healthier diet and participate in increased physical activity may address some of the documented perceived barriers to positive change, such as perceived cultural reasons, the monotony of exercise, and the lack of family support.

To our knowledge, no study has investigated the effect of a family-based diet and exercise intervention in the UAE. The EHHP is such an intervention that has adapted the DPP, which is based on individual participation and North American cultural values, into a family-based, culturally and religiously sensitive program with intensified access to a health coach. This trial is intended to assess whether a family-based program may result in better uptake and adherence to proven lifestyle-based interventions than the internationally standard, individual-based care that is currently offered as usual care. This may inform policy changes, allocation of resources, and future research addressing the leading cause of mortality in the UAE.

### Objectives

Research hypothesis: The EHHP, a family-based diet and exercise intervention using a family health coach with technological aids, reduces cardiovascular risk factors when compared to the current usual management of obese and overweight patients in the emirate of Abu Dhabi, United Arab Emirates.

#### Study objectives

*Primary objective*. To determine if the EHHP reduces weight and BMI in obese and overweight Emiratis.

*Secondary objectives*. To determine in obese and overweight Emiratis, if the EHHP has significant effect in:

Reducing systolic and diastolic blood pressure;Reducing hemoglobin A1c;Reducing total cholesterol, LDL cholesterol and triglycerides;Increasing HDL.Decreasing waist circumferenceDecreasing BMI

## Methods and analysis

This protocol is being reported using the SPIRIT (Standard Protocol Items: Recommendations for Interventional Trials) and TIDieR (Template for intervention description and replication) framework and checklists (S1 and S2 Appendices).

### Trial design

Due to the family-based nature of the intervention package, the EHHP is designed as a stepped-wedge cluster randomized trial. Each cluster receives the intervention at a randomized time, which causes them to crossover from control to intervention. This type of study design has logistical advantages as well as having utility in evaluating the group-level impact of interventions that have been proven effective in individually randomized trials [13, 14]. There exists an extensive literature on the conduct, benefits, and limitations of stepped-wedge studies, some of which is available as open-source [15]. For an expanded discussion of the specific benefits and limitations in the context of the EHHP, please see the discussion section. The EHHP itself is based on the Diabetes Prevention Program, which has shown both short- and long-term benefit in multiple individual randomized control trials [16, 17].

Patients that present to Kanad Hospital with a BMI that meets inclusion criteria who give consent (S3 and S4 Appendices) for participation will be asked to invite other extended family members to participate. Participants will then provide contact information for family members to schedule appointments at Kanad Hospital for eligibility screening according to inclusion and exclusion criteria. Those meeting criteria will be invited to participate in the study and consent will be obtained. For logistical purposes, a minimum of eight participants per family will be required for enrollment. Once the family is enrolled, baseline measurements will be obtained.

Once the prespecified number of family clusters are enrolled, they will be randomized by the statistical team (NN, [name]) using random number generation and assigned a number 1 through n, where n is the number of clusters. This number will be communicated to the health-coach by encrypted message and will provide order of intervention [18], with a cluster entering the intervention at each time as a cohort to maximize study power (Figs 1 and 2) [19].

**Fig 1 pone.0282502.g001:**
[figure not shown]
SPIRIT schedule of stepped intervention.

**Fig 2 pone.0282502.g002:**
[figure not shown]
Graphical timeline of stepped intervention.

Prior to being exposed to the intervention, the participants will be exposed to usual care which will comprise scheduled individual visits with a dietician, who will recommend individualized diet and exercise modifications. As noted below, individuals undergoing or planning to undergo either bariatric surgery or the use of weight-loss pharmacotherapy are not eligible to participate in this study. The available medications in our location include liraglutide, semaglutide, and orlistat.

Each cluster will thus be exposed to the intervention in a stepped fashion. The intervention, which will be described in further detail below, will take approximately 16 weeks to complete. Pre-intervention measurements will be taken approximately every 16 weeks until the cluster enters the intervention phase. These measurements will be compared with post-intervention measurements at the conclusion of the intervention to assess for a statistically significant difference. The specific type of trial is a closed cohort, complete stepped-wedge cluster randomized trial [13]. This study protocol has been approved by the Kanad Hospital Research Ethics Committee on March 16, 2021 with the assigned authorization #2012.15. Approval of amendments and renewal were given on March 16, 2022 with the same assigned authorization number.

#### Statistical analysis

A mixed (random + fixed effects) linear model will be used where the parameters (e.g., BMI) measured at the end of each 16-week episode will be the outcome (dependent, y variables) values. These will be analyzed such that baseline values (measured just prior to the start of an episode) will be fixed covariables, as well as whether the episode was an "intervention" or "control" episode. Random effects are the family units.

Episodes after the intervention episode will be excluded from the main analysis and used to explore the persistence of intervention effects.

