## Discussion

Although previous surveys and reported data have defined the scope of the problem of deaths related to obesity and CVD in the UAE and have suggested possible underlying lifestyle-related etiologies, this would be, to our knowledge, the first prospective interventional trial utilizing the strength of family relationships to affect positive lifestyle change.

There is a lack of prospective studies in our setting, which is traceable, at least in part, to the difficulties in conducting robust studies. Previous studies have fallen victim to higher-than-expected rates of drop out and loss to follow up, funding for studies is difficult to obtain and utilize due to multiple organizational restrictions and limitations, and privacy and ethical concerns inhibit the participation and of, and collaboration between, larger organizations within the health system.

In an ideal scenario, this vital research question would be investigated using a cluster randomized control trial with family clusters matched for the presence of confounding factors such as age, obesity, presence and severity of diabetes, hypertension, and hyperlipidemia. It would be a multicentric trial that applied the intervention simultaneously for all family clusters to avoid the confounding effects of time and contamination. In addition to the previously mentioned restrictions, our specific limitations include insufficient funding to utilize more than one health coach, a grant period of 2–3 years, and limited administrative support.

The EHHP team decided that despite these limitations, the study should proceed with the best possible protocol under these conditions. Therefore, a pragmatic study design utilizing a stepped wedge of clusters was selected to mitigate these restrictions. The stepped nature of the intervention allows statistical analysis (using mixed models) that utilize both differences in weight and other target parameters between time periods before and after intervention, and differences between clusters (comparing clusters under intervention with those not yet having received the intervention). This allows an efficient estimation of the impact of the intervention on target parameters and to test whether this impact is statistically significant. This may inform and benefit follow on studies.

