The study focuses on the primary outcome of weight as well as secondary outcomes which consist of simple measures of CVD risk. Despite the importance of additional data, the team lacks the resources to obtain intake of whole grains, ultra-processed foods, and red meat. As the primary outcome in this study is change in weight, which is most directly correlated to change in caloric intake and expenditure, we have prioritized accurate recording of caloric intake accordingly. Unfortunately, our grant does not allow us to bring a dietician onto our team. The software that comes with the fitness tracker allows the participant to enter their dietary intake into their smartphone, but it excludes commonly eaten foods in our setting and is not available in the Arabic language at this time. Due to the anticipated amount of missing data, we have decided to exclude a diet diary in this iteration of the study despite the richness of information that could be collected. The investigators have elected not to run multiple clusters simultaneously, allowing the health coach to be focused on one to two families at a time. Although we are studying family clusters, these clusters represent extended families that may be spread across a geographic area of several hundred square kilometers; the afternoons after Friday prayers are the optimal time to gather and address the extended family as a group. This restricts the time available for group sessions to a few hours a week, and thus limits the number of clusters a single health coach can effectively manage. This opens up the possibility of changes over the course of the study in the clusters that are randomized to later intervention episodes; their willingness to participate may have waned, leading to increased losses, or the families may have chosen other approaches for weight loss, leading to contamination.

An additional limitation that stems from our inability to fund multiple health coaches is that any result becomes difficult to generalize to approaches using multiple health coaches or infer how such coaches should be selected and trained. This makes the external validity of our findings uncertain and would require larger, better resourced studies to investigate.

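### The stated primary model has no calendar-period term, so season or a changing rate of weight change is partly counted as intervention effect, in either direction

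*Protocol article*

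**What the plan says.** The Trial design section (text after Fig 2) describes a "closed cohort, complete stepped-wedge cluster randomized trial". All families are enrolled before the order is randomised, so they share one calendar of 16-week episodes.

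The Statistical analysis section sets out the model. The outcome is the value at the end of each episode. On the fixed side, the values taken at the start of each episode "will be fixed covariables, as well as whether the episode was an" intervention or a control episode. On the random side, "Random effects are the family units". It adds: "Episodes after the intervention episode will be excluded from the main analysis". The Abstract describes the same model, also without a time term.

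The Discussion treats time as a threat. The ideal trial would have "applied the intervention simultaneously for all family clusters to avoid the confounding effects of time and contamination". Of the design actually chosen it says: "This opens up the possibility of changes over the course of the study in the clusters that are randomized to later intervention episodes", and it gives waning willingness and other routes to weight loss as examples. It also says that the analysis will use "differences between clusters (comparing clusters under intervention with those not yet having received the intervention").

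**The concern.** In a stepped wedge, exposure and calendar time are linked by construction. Randomising the order protects the comparison only when treated families are set against families that are untreated in the same period. A model with an exposure indicator and no period term pools all control episodes whatever their date, so it does not isolate the concurrent contrast that the Discussion describes.

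The article itself gives reasons to expect change over time: heat that limits outdoor exercise for part of the year (Introduction), and the waning and contamination named in the Discussion. What is at stake is the primary estimate of weight change. The secondary outcomes share the same model.

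**Working it through.** **Inputs from the article.** Target reduction 7%, SD of family-mean change 3.5%, one-sided 5%, 80% power, 10 families (Sample size); 16-week episodes (Trial design); analysed episodes are the control episodes plus one intervention episode per family (Statistical analysis).

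**The plan's own figure.** Four clusters per arm gives noncentrality 7 / (3.5 × √(2/4)) = 2.83 on 6 degrees of freedom, and exact one-sided power of 80.2%. The figure reproduces. It comes from a parallel-arm t-test, so it says nothing about period adjustment.

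**Assumptions.** The number of steps is not clear. Trial design has one cluster entering at each time; Participant timeline has one to four pre-intervention assessments, which implies about four sequences. Several layouts were therefore computed. The four-sequence layouts place 3, 3, 2 and 2 families, with 0–3 control episodes (if the enrolment assessment counts as the first) or 1–4 (if it does not). The size of any drift or season and the within-family correlation ρ are assumed.

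**Method.** Weight is adjusted for its value at the start of the same episode, so with a slope of 1 the model compares 16-week changes. For a pattern m of expected changes with no intervention effect, the bias is the exposure element of (X′V⁻¹X)⁻¹X′V⁻¹m, where V has variance 3.5² and correlation ρ within family. At ρ = 0 this is the difference in mean m between intervention and control episodes.

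**Constant trend.** The change is the same in every episode, so m is a constant and goes into the intercept. Bias is 0.00 in every layout.

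**Change drifting by 0.5 points per episode (assumed).** At ρ = 0 the bias is 0.5 × the gap in mean period.

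| Layout | Mean period, control | Mean period, intervention | Gap | Bias, ρ=0 | Bias, ρ=0.3 | Bias, ρ=0.9 |
|---|---|---|---|---|---|---|
| 10 steps × 1 family | 165/45 = 3.67 | 5.50 | 1.83 | 0.92 | 1.25 | 1.55 |
| 5 steps × 2 families | 40/20 = 2.00 | 3.00 | 1.00 | 0.50 | 0.67 | 0.89 |
| 4 sequences, 0–3 control episodes | 21/13 = 1.62 | 2.30 | 0.68 | 0.34 | 0.49 | 0.72 |
| 4 sequences, 1–4 control episodes | 44/23 = 1.91 | 3.30 | 1.39 | 0.69 | 0.79 | 0.86 |

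The bias takes the sign of the drift. With categorical period terms it is 0.00 in every cell.

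**Annual season of amplitude 1% (assumed).** At the worst start date and ρ from 0 to 0.3, the bias is ±0.21–0.31 points (10 steps), ±0.26–0.47 (4 sequences, 0–3) or ±0.67–0.69 (4 sequences, 1–4). About 0.2 to 0.7 of the amplitude leaks through, with a sign that depends on the start date.

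**Cost of period terms.** At ρ = 0 with 10 steps, the SE without period is 3.5 × √(1/45 + 1/10) = 1.22; with period it is 1.32. With 5 steps, 3.5 × √(1/20 + 1/10) = 1.36 becomes 1.50. For ρ from 0 to 0.3 the rise is roughly 8–20% in the first three layouts, and 20% to just over 30% in the fourth. The largest SE with period terms is about 1.60. Since 7 / 1.60 = 4.4, power for the 7% target stays above 99%.

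**The case against.** **The article may be condensed.** It does not say that its listed terms are the only ones, a fuller analysis plan may exist, and the Discussion plainly intends a comparison with families not yet treated. This stands in part. But the section does not leave the model open: it names the fixed terms and the random term, and the Abstract agrees. Followed as written, that model does not deliver the Discussion's comparison.

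**The drift is arbitrary, and large over ten steps.** Half a point per episode starting from zero accumulates to 0.5 × (0+1+…+9) = 22.5 points under usual care, and the Introduction calls obesity rates stable. Ten steps of 16 weeks also take 160 weeks, beyond the 2–3 year grant. This stands. The 10-step row is an upper illustration, and the 4- and 5-step rows are the better guide.

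**Stronger readings do not hold.** A reader might infer three further things:

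- That any trend in weight is counted as effect. It is not: each episode is adjusted for its own starting value, so a steady trend cancels.
- That dropping post-intervention episodes widens the time gap. It narrows it. With 10 steps, keeping them as exposed gives 7.00 − 3.67 = 3.33 periods, against 1.83 without them; with 5 steps, 1.67 against 1.00.
- That regression to the mean after selection on BMI favours the intervention. An extra 1-point loss confined to the first episode shifts the estimate by about 0.1 to 0.5 points against it (ρ from 0 to 0.5). Loss that fades as willingness wanes would act in the same direction.

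**Conclusion.** The point holds in this limited form. The omission is clear from the text; the size of the bias is not, because the documents give no drift or season. Under the assumed half-point drift, the 4- and 5-step figures are about 5–13% of the 7% target (0.34/7 to 0.89/7). That would not hide or create an effect of the planned size, but it would distort the estimate, and it would matter for the test if the true effect were much smaller. Outside weight-loss efforts that grow over time would flatter the intervention, fading willingness would work against it, and season could do either.

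The cancellation of a steady trend assumes a slope near 1 on the starting value, which is reasonable for weight over 16 weeks. The documents do not support saying that the primary result will be spurious, or in which direction it will err.

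**What to change.** Add the 16-week calendar period as a categorical fixed effect to the primary weight model and to every secondary model. If steps turn out to be sparse, for instance one family each, use a simpler calendar-time term and say so; it removes only the shape of trend that it models.

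State that the intervention effect is the within-period contrast between families in their intervention episode and families still in control. Note that, under the exclusion rule, a last step without concurrent controls adds little to the estimate. State the number of steps and families per step as well, by reconciling Trial design with Participant timeline, since that fixes how many period terms are needed.

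The change is a few lines of text and needs no new data. The price is the loss of precision shown above, which the planned 10 families can carry under the plan's own 3.5% and 7%.

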#### Sample size

In order to calculate an appropriate sample size without reliable information on the intracluster correlation we will calculate our sample size in terms of the number of clusters required. This also takes into account the cluster design of the study. The sample size in terms of individuals will then be the required number of clusters times the average cluster size.

For this purpose, we assume that the natural fluctuation in cluster mean weight change (i.e., the standard deviation in mean weight change among clusters) is 3.5%, i.e., half the target weight reduction of 7%. This assumption is based on (or rather inspired by) variation in BMI between successive waves (approximately 5 years apart: much longer than our follow-up period) observed in the Framingham Study [29] where the standard deviation in individual weight differences was between 6% and 7%.

We will assume that we compare the two groups using an unpaired t-test.

For a two-armed parallel cluster randomized design to achieve a power of 80% and a one-sided significance level of 5%, we would need four clusters in each trial arm, i.e., a total of eight clusters [32] Since the stepped-wedge cluster design that we have selected is more efficient than a parallel design [33], this sample size should be adequate given our assumption. However, to accommodate for unduly optimistic assumptions about the standard deviation in weight changes we will increase our total sample size to 10 clusters.

An interim analysis will be performed once four clusters have completed the intervention and the required sample size will be re-calculated on the basis of observed fluctuations in parameters; if this leads to the conclusion that more than 10 clusters are required to detect a statistical significance in the primary outcome, the team will meet to discuss how and if the sample of clusters can be extended.

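### With family as the only random effect, the model has no term for a shift shared within one episode or for repeat measures on a person, so its error bars are most likely too narrow

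*Protocol article*

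**What the plan says.** The Statistical analysis section specifies a mixed linear model in which the parameters "measured at the end of each 16-week episode will be the outcome (dependent, y variables) values". The fixed covariables are the value just before the episode and whether the episode was intervention or control. The random part is one sentence, which also stands in the Abstract: "Random effects are the family units". Episodes after the intervention episode are left out of the main analysis, so each family contributes one intervention episode.

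The Trial design section says of the same people's repeated measurement: "The specific type of trial is a closed cohort, complete stepped-wedge cluster randomized trial". It also sets a minimum of eight participants per family.

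The Sample size section gives no intracluster correlation and works from family means: "we assume that the natural fluctuation in cluster mean weight change" has an SD of 3.5%, half the 7% target. As background it cites an outside cohort in which "the standard deviation in individual weight differences was between 6% and 7" per cent. It assumes an unpaired t-test with 80% power at a one-sided 5% level, giving four clusters per arm, raised from eight to 10 in total.

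**The concern.** Because the episode-start value is a covariable, the model in effect describes change over an episode. A family term, read plainly as a family intercept, then captures only a tendency to gain or lose that lasts through all of a family's episodes. Given that term, the eight or more relatives measured in one episode count as independent.

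The article itself gives reasons to expect relatives to move together within an episode. The Introduction describes communally prepared meals and a collective family commitment, and one health coach treats the family as a group. With a single intervention episode per family, such a shift cannot average out over episodes within that family.

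The same people also recur across episodes without a participant term. Both omissions affect the standard error of the primary effect. The same model sentence covers the secondary outcomes, although the article has no variance figures for them.

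**Working it through.** **1. The article's sample size.** Inputs from the Sample size section: difference 7%, SD of family mean change 3.5%, one-sided 5%, power 80%.

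n per arm ≈ 2 × (1.645 + 0.842)² × (3.5/7)² = 3.09, so 4. The exact t-test with 4 per arm has 80.2% power (64.5% with 3). The stated four per arm is reproduced, so the design does rest on the noise in family mean change.

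**2. Variance components (assumption).** Treat 3.5% as the SD of a mean of 8 people whose individual SD is s:

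(3.5/s)² = (1 + 7 × ICC)/8

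- s = 6: ICC 0.246, design effect 1 + 7 × ICC = 2.72
- s = 6.5: ICC 0.189, design effect 2.32
- s = 7: ICC 0.143, design effect 2.00

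At s = 6.5 the family-level SD is 6.5 × √0.189 = 2.82% and the within-family SD is 6.5 × √0.811 = 5.86% (up to rounding).

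**3. Hand check of the worst case.** If all family-level variance is specific to the episode, a family mean has a true SD of 3.5%. Treating its 8 members as independent gives 6.5/√8 = 2.30%, a ratio of 0.657. The 1.645 cutoff then acts as 1.645 × 0.657 = 1.08, an upper tail of 14%.

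**4. Null simulation of the stated model.** Individual data, REML, family random intercept, episode-start value and intervention indicator as fixed effects, normal cutoff, no time trend, 10 families of 8, s = 6.5. The Participant timeline allows one to four pre-intervention assessments, so schedules with 0-3 and 1-4 control episodes were run; 0-9 was added for one family per step.

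With all family-level variance episode-specific, the reported SE against the true SD of the estimate was:

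- 0-3 control episodes: 0.98 against 1.53
- 1-4 control episodes: 0.85 against 1.31
- 0-9 control episodes: 0.81 against 1.20

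The reported SE is about one third too small, in line with step 3.

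One-sided rejection at nominal 5%:

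| Family variance that is episode-specific | No lasting person-level variance | Half of individual variance lasting by person |
|---|---|---|
| All | 13-15% | 12-13% |
| Half | 10-11% | 6-10% |
| One fifth | 8-9% | 4-5% |
| None | about 5% | 1-2% |

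In the top left cell the two-sided 5% test rejects 18-20% of the time. Eight is the minimum family size: at 20 per family, with the same variance components, that cell becomes 21-22% one-sided. In the bottom right cell the SE is too large (0.93 against 0.71 with 0-3 control episodes, 0.78 against 0.57 with 1-4).

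**5. The alternative.** Family-by-episode mean change with a family random effect and a t cutoff gave 4.2-6.8% one-sided in every setting with an episode-specific share above zero (no lasting person-level variance). With all family variance episode-specific and 8 per family, its one-sided power at a 7% effect stayed above 99%.

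**The case against.** The strongest reply is that the Sample size section does not contradict the model. It gives one SD for one change per family, and a single-period SD cannot separate a lasting family tendency, which the family term handles, from an episode-specific one. This stands. A reader might infer that the article assumes episode-specific variance. The word fluctuation and the successive-wave source lean that way but do not settle it, and if the variance is wholly lasting and people show no lasting differences, the stated model is correct.

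It also stands that the ICC is derived here, not stated. The article disclaims reliable information on it, and its individual SD comes from waves about five years apart.

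Other stronger readings fail:

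- A reader might infer that the effective sample size is close to 10. A design effect of 2.0-2.7 on 80 people leaves about 80/2.72 = 29 to 80/2.00 = 40.
- A reader might infer that the missing participant term adds false positives. The main contrast compares the same people's control and intervention episodes, so omitting lasting personal differences makes the SE too large.
- Holidays or fasting might be offered as the mechanism. The document names neither, and as calendar events common to all families they would be a period effect.
- The normal cutoff was a choice made for the check. The article names no reference distribution, so its absence is no fault in itself.

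Finally, a model run on family means would carry the episode-specific noise in its residual. The article does not say that it is run that way. The random structure is stated twice, so it is not merely a detail left to an unseen analysis plan.

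**Conclusion.** The concern holds in a conditional form. As written, the model gives correct error bars only if family-level variance in weight change is wholly lasting and people have no lasting differences of their own, or if the two omissions happen to cancel. Otherwise the intervals are wrong. They are most likely too narrow, with one-sided error up to about 13-15% for families of 8 at s = 6.5, but they can be too wide, with error down to 1-2%. The size rests on two shares that the article does not give, on an ICC of about 0.19 derived from its figures, and on a normal cutoff. The damage is to interval width and type I error. Power at the 7% target is not affected. For the secondary outcomes the structural gap is the same, but its size cannot be computed from this document. This should be fixed before analysis.

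**What to change.** In the Abstract and the Statistical analysis section, replace the family-only random effect with three: family, family-by-episode, and participant within family. State small-sample degrees of freedom (Kenward-Roger or Satterthwaite). An acceptable alternative is to analyse family-by-episode means with a family random effect and a t reference distribution.

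The cost is a change of wording and a few lines of code, with no new data and no change in trial conduct. The downside is that intervals may be somewhat wider.
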